# The effectiveness of a tablet-based video game that stimulates cognitive, emotional, and social skills in developing academic skills among preschoolers: study protocol for a randomized controlled trial

**DOI:** 10.1186/s13063-022-06875-9

**Published:** 2022-11-09

**Keywords:** Cognitive skills, Emotional skills, Academic skills, Tablet play, Preschools, Randomized controlled trial

## Abstract

**Background:**

Evidence suggests that children from low-income families begin the preschool stage with less academic and non-academic skills development compared to higher-income families. There are several successful experiences of early stimulation of cognitive and social-emotional skills; however, there is scarce evidence of the effectiveness of a video game that incorporates the stimulation of these skills simultaneously. This study aims to evaluate the effectiveness of a video game in stimulating cognitive, emotional, and social competence skills in developing academic skills in socioeconomically disadvantaged preschool children.

**Methods:**

A cluster-randomized controlled trial design will be used. A tablet-based video game that stimulates cognitive and socio-emotional skills to improve the development of academic skills is compared with a tablet-based game where students draw and paint with no explicit stimulation of cognitive and socio-emotional skills. Eighteen schools and 750 Chilean preschool students will be recruited. The effectiveness of the intervention will be assessed using a direct evaluation of children on literacy learning and pre-calculation skills at baseline, immediately after stimulation, and at 6, 12, 18, and 24 months post-intervention. The mediating effect of working memory, inhibitory control, emotion recognition, and prosocial behaviours will be assessed on the effectiveness of the intervention.

**Discussion:**

The proposed study will be the first to test the effectiveness of a tablet-based video game stimulating cognitive and social-emotional skills to improve academic skills in socioeconomically disadvantaged preschool children in Chile, controlling for gender, age (in months), mental health, and baseline conditions of stimulated skills.

**Trial registration:**

ClinicalTrials.gov NCT05224700. Registered on February 2022

## Administrative information

Note: the numbers in curly brackets in this protocol refer to SPIRIT checklist item numbers. The order of the items has been modified to group similar items (see http://www.equator-network.org/reporting-guidelines/spirit-2013-statement-defining-standard-protocol-items-for-clinical-trials/).

## Introduction

### Background and rationale {6a}

Several authors [1] have expressed that improving learning and socialization skills has many advantages in the prevention of behaviour problems, the quality of life of children, and long-term health and economic outcomes. Evidence suggests that children from low-income families may begin the preschool stage with lower development of academic skills (such as precalculus and initial literacy) and non-academic skills (such as emotional and social competence), when compared to children from higher-income families [2]. Such differences could increase long-term social-emotional, educational, and health disparities [3]. Between the ages of 3 and 7, critical aspects of human development happen, such as emotion recognition, control of behaviour [4], and the development of Executive Functions (EF) [5]. Therefore, it becomes essential to stimulate these skills among socially vulnerable children.

The EFs are integrated by different components participating in goal-directed behaviour, where inhibitory response, attention, and working memory seem critical [6]. In recent years, the development of EFs has been a significant focus of research, among other reasons, because [6] (a) there is growing evidence that EFs are crucial to school success; (b) EFs are deficient in several learning/developmental disorders; (c) children in socioeconomically disadvantaged context seem to have lower EF development before entering formal education when compared when their counterparts from more affluent families; and (d) there is increasing evidence that EFs can be stimulated in children with typical and atypical development.

Within EFs, working memory (WM) and inhibitory control (IC) have been identified as critical components in the development of academic skills such as early literacy and precalculus [7], in addition to the evidence that they can be stimulated early in development [8]. WM and IC can be developed if they are stimulated directly; however, it is less clear, especially for WM, the impact of their stimulation on the development of other skills such as literacy and precalculus [9–11]. Studies have also found the relationship between EFs and other behavioural and non-cognitive skills [12], such as social [13] and emotional development [14].

Emotional understanding refers to the fashion children identify, predict, and explain emotions regarding themselves and others. Around 3 years of age, children can start labelling emotional expressions. Then, they rapidly continue to advance in the development of emotion recognition. Rosnay et al. [15] have reported that children who are more successful in understanding emotional cues are more likely to develop social skills and prosocial responses to their peers and to form positive interpersonal relationships that encourage adaptation to social situations. With regard specifically to social ability and behaviour involving the other, it becomes necessary to divide components into those inherent to the person, with those that are dyadic. We will dwell on the precursor elements of a personal level, such as the ability to identify and monitor related behaviours, closely linked to emotional and executive functions [16]. In this sense, several studies have observed that the development early in the life of early emotional and social competencies facilitates the successful interactions of children with others and favours better academic achievements and mental health [17, 18].

In general, interventions that stimulate emotional and social skills include varied strategies and practices that are usually not limited to promoting a particular skill. Therefore, it is difficult to isolate the effect of the stimulation of a specific skill. A meta-analysis by Blewitt et al. [19], which included the revision of programmes for children between 2 and 6 years old, found that children exposed to social and emotional stimulation interventions showed a significant improvement in social and emotional competencies, learning, behavioural regulation, and decreased their emotional and behavioural problems. Most of the revised interventions have been studied in developed countries, are complex, sustained in time, and require a lot of resources in personnel and material that are not readily available in vulnerable socio-economic contexts.

In recent years, there has been a growing use of devices with touch screens by children. It has been observed that their use in an educational context for academic purposes has favourable evidence [20], especially when these applications have been created with careful designs and content selection [21]. A recent systematic review by Griffith et al. [22] concludes that there is evidence that interactive applications can be helpful and accessible tools to support early academic development. Herodotou [23] found that most of the research involving technological devices evaluated cognitive aspects and, in general, neglected the socio-emotional aspects. In addition, of the studies analysed, which report results in various areas of children’s development, eight present findings in the development of academic skills, evidencing advances that guide the contribution of devices with touch screens in these skills, that is, in learning.

Finally, there are several successful experiences of early stimulation of cognitive skills using technological devices, such as COGMED for children aged 7–17 years with ADHD by Klingberg et al. [24], and Memory Booster for children aged 5 to 8 years of St Clair-Thompson and collaborators [8]. Other interventions promoting socio-emotional skills using interactive teaching strategies have also accumulated good evidence, such as PATHS created by Greenberg and collaborators [25] and Incredible Years by Carolyn Webster-Stratton [26]. However, we did not find an evaluation of the effectiveness of a programme that incorporates the stimulation of cognitive and social-emotional skills using an interactive video game on a tablet for preschool children, followed up in the medium term.

## Objectives {7}

The main objective of this study is to assess the effectiveness of a programme of stimulating cognitive skills (working memory and inhibitory control), emotional skills (recognition of emotions), and social competence (choice of prosocial behaviours), in the development of academic skills of initial literacy and precalculus in socioeconomically disadvantaged preschool children. The outcomes will be assessed immediately after the intervention, at 6, 12, 18, and 24 months post-intervention, controlling for gender, age (in months), mental health, and baseline conditions of the stimulated skills.

The specific objectives are (a) to determine the acceptability and ease of use of the programme of stimulation of cognitive, emotional, and social competence skills in socioeconomically disadvantaged preschool children; (b) to evaluate the changes in the variables working memory, inhibitory control, emotion recognition, and the choice of prosocial behaviours, in both groups (intervention and comparison group), immediately after the intervention and at 6, 12, 18, and 24 months post-intervention; (c) to determine the effectiveness of the programme of stimulation of cognitive, emotional, and social competence skills in the development of the academic ability of early literacy and in the development of the academic skill of precalculus in socioeconomically disadvantaged preschool children, immediately after the intervention and at 6, 12, 18, and 24 months post-intervention, controlling for gender, age (in months), mental health, and baseline conditions of the stimulated skills; and (d) to explore the influence of potential mediators (working memory, inhibitory control, emotion recognition, and choice of prosocial behaviours) on the observed effects of the cognitive, emotional, and social competence skill stimulation programme, controlling for gender, age (in months), mental health, and basal conditions of the stimulated skills.

We hypothesize that the programme will have high acceptability among socioeconomically disadvantaged preschool children. Immediately after the end of the intervention, there will be an improvement in the variables working memory, inhibitory control, recognition of emotions and choice of prosocial behaviours, with greater development in the intervention group, which will be maintained throughout the different measurements. The same will happen in developing early literacy and precalculus academic skills. The effect of the programme is mediated by working memory, inhibitory control, emotion recognition, and choice of prosocial behaviours, controlling for gender, age (in months), mental health, and baseline conditions of stimulated skills.

## Trial design {8}

This is a cluster randomized controlled trial, parallel-group type, where the tablet-based video game stimulating cognitive, emotional, and social skills is compared to a tablet-based video game involving only painting. The effectiveness of this programme will be evaluated by one pre-stimulation measurement, and five post-stimulation measures, immediately after stimulation, at 6, 12, 18, and 24 months. The patient allocation is randomized with a ratio of 1:1. See Fig. 1.

**Fig. 1 Fig1:**
[figure not shown]
Flowchart

## Methods: participants, interventions, and outcomes

### Study setting {9}

This study will be carried out in schools with preschool education located in two cities in the Maule region (Talca and Linares), Chile.

### Eligibility criteria {10}

#### Inclusion criteria

Establishments with an index of school vulnerability (ISV) ≥70% (based on the information provided by participating families)Establishment that offers preschool and elementary educationEstablishment located in the region of Maule, ChileMixed-sex schools.Classes with a minimum of 15 students each

#### Exclusion criteria

School is implementing a similar programme.Special education school.Children with a reported cognitive disability.

### Who will take informed consent? {26a}

All schools in Region del Maule will be assessed for eligibility. The eligibility of schools to participate in this study will be evaluated based on the abovementioned criteria. After the schools have been considered eligible, all eligible schools will be invited. Then, the principal of the selected schools will receive the study information. After school officials agree to participate in the study and sign an authorization form, preschool educators and pre-kindergarten assistants will be invited to participate (in conjunction with kindergarten and first-grade educators as part of the longitudinal study). Subsequently, the parents or guardians of the students will be informed about the study in a meeting and invited to participate. Along with this information, parents will receive the informed consent form and must sign it if they agree to have their children participate in the study. Finally, all authorized children will be asked for their willingness to participate in the study. Even if you have the consent of children, if the child does not confirm that they want to participate, they will not be forced.

### Additional consent provisions for collection and use of participant data and biological specimens {26b}

No samples were collected. There are no plans for future studies using data collected in this trial.

### Interventions

#### Explanation for the choice of comparators (6b)

The control group (active) will not work with the programme of stimulation of cognitive skills and socio-emotional; instead, this group will use a tablet-based game where they must paint during the 20 sessions of 30 min, two times a week. At the end of the activity, you will be given a sticker for your participation. In this group, the educators will have the same training in cognitive, emotional and social competence skills as those in the intervention group. They will also be trained in using the game to paint, and meetings will be held every 15 days to evaluate possible doubts. This way, an attempt to avoid the effects of the programme dependent on the educators is made since, in both groups, a similar treatment would be received. The knowledge will remain within the educational institution for future work in the area. Like the intervention group, the group will be guided by the kindergarten educator responsible for the course and will work with the entire course group simultaneously (each child will have an individual tablet with headphones). All children who wish to play will be able to participate (to avoid discrimination); however, only children who have parental/guardian consent and the consent of the child themselves will be evaluated. A research team member will be present at each session to ensure that the session flows correctly.

#### Intervention description {11a}

The intervention group will use the tablet-based video game to stimulate cognitive and emotional skills and social competence. The intervention will be implemented through a tablet game programme that promotes cognitive skills (working memory and inhibitory control), emotional (recognition of emotions), and social competence (choice of prosocial behaviours) individually in the classroom context. This programme will be held during the academic year during school hours and has 20 sessions of 30 min, two times a week (in total two and a half months), where students will be in groups in the room, but each child will work with a tablet with headphones individually. At the end of the activity, each child will receive a sticker for participation. All activities are games with the following structure: an introduction with instructions and selection of the protagonist (avatar: which can be modified according to hair colour, skin, sex, and clothes, who speaks directly to the child), followed by a practice exercise to make sure that the children understand what they should do (it is repeated until the child performs the routine correctly), and finally, the stimulation activity (4 different activities with five exercises each). In the first ten sessions, working memory and emotion recognition are stimulated together (4 activities for each skill in each session). In the remaining ten sessions, inhibitory control and the choice of prosocial behaviours are stimulated.

#### Criteria for discontinuing or modifying allocated interventions {11b}

The students of the intervention and comparison group will participate in all the programme sessions; however, the data of the children with cognitive disabilities (with previous diagnosis) will not be considered for the analyses. Children with cognitive disabilities, in the context of this study, are those children who have been identified by a trained school professional indicating that they cannot clearly understand the instructions of the instruments. The main reasons for excluding these children from the analyses are that the measurement tools are not validated for children with cognitive disabilities. These children may have difficulty understanding the instructions making the results less reliable.

In addition, while students cannot leave the classroom if they do not want to participate in the sessions, they can leave the study at any time and for any reason, if they wish, without any consequences. If children leave the study, their information and collected data will not be analysed.

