### Concealment mechanism {16b}

After the randomization and allocation, schools will be informed by a research assistant of the group belonging by email and confirmed by telephone. Each school will only receive their information of allocation. Additionally, this information will not be disclosed to the assessment research team (outcome evaluators) to keep them blind to the schools’ allocation.

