### Procedure for unblinding if needed {17b}

For the nature of the intervention, the participants will know the allocation of the school.

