## Statistical methods

### Statistical methods for primary and secondary outcomes {20a}

First, descriptive analyses will be performed to evaluate the balance of variables between groups at the beginning of the study. The primary analysis will be conducted based on intention-to-treat. This analysis includes all randomized subjects in the groups, regardless of whether or not they complete the treatment or follow-up period. Multivariate regression models of mixed effects will be carried out considering as a dependent variable the performance in the tests of academic skills (initial literacy and precalculus) and as an independent variable belonging to the intervention or comparison group, controlling for gender, age (in months), mental health, and performance in the same tests in the baseline evaluation. Regression models will consider the nested nature of the data (clustering), since students’ performance within the same educational establishment tends to be correlated. While primary outcomes will be considered as those obtained after the intervention, analyses will be repeated for follow-up at 6, 12, 18, and 24 months. This will allow for evaluation of the maintenance of the effect of the intervention until first grade. We will use mixed-effect regression models of repeated measures to assess convergence and divergence between groups in follow-up times. Subgroup analyses will be performed for the primary outcome variable using interaction terms in the regression models between the randomized groups and the gender variable. This will allow us to evaluate the moderating effect. Sensitivity analyses will also be performed to assess the impact of lost data using multiple imputations. The results with and without imputed data will be presented and compared. The tests will be done with Stata 15.0.

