### Methods in analysis to handle protocol non-adherence and any statistical methods to handle missing data {20c}

The primary outcome will be assessed using an intention-to-treat analysis. Every participant randomized to the trial will enter the primary analysis. Accordingly, participants who drop out prematurely, or are non-compliant with the study intervention, will be included in the primary analysis within the respective group they have been assigned to at randomization. Multiple imputations will be used to handle missing data in the primary and secondary analyses.

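### The rules for leaving children with cognitive disability out of the analysis do not match, and the loosest one is not tied to a time before allocation is known or to a blinded judge

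*Protocol article*

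**What the plan says.** Three places in the protocol article describe the children concerned.

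- Exclusion criteria: "Children with a reported cognitive disability".
- Section {11b}, first statement: "the data of the children with cognitive disabilities (with previous diagnosis) will not be considered for the analyses".
- Section {11b}, next sentence, given as the meaning of the term for this study: children "identified by a trained school professional indicating that they cannot clearly understand the instructions of the instruments". The reason offered is that the tools are not validated for such children and their results would be less reliable.

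The same section says that "The students of the intervention and comparison group will participate in all the programme sessions", so these children are in the classroom in both arms and the rule acts on their data.

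The analysis sections make no exception for them. Section {20a} says "This analysis includes all randomized subjects in the groups, regardless of whether or not they complete the treatment or follow-up period", and {20c} says "Every participant randomized to the trial will enter the primary analysis".

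On who knows the arm, {16b} says "After the randomization and allocation, schools will be informed by a research assistant of the group belonging by email and confirmed by telephone", and {17b} says "the participants will know the allocation of the school". Section {17a} blinds the outcome evaluators and the data analyst; school staff are not named.

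**The concern.** A child can meet one of these rules and not another. A child with no diagnosis whom a school professional thinks cannot follow the tests is caught by the last rule only. A child with a diagnosis who follows the tests well is caught by the diagnosis rule but not by the definition that is meant to explain it. Two analysts could build different populations from the same data.

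The last rule matters most. It asks whether the child can follow the instruments, and those instruments include the literacy and pre-calculation tests that form the primary outcomes. Children judged unable to follow a test are likely to score low on it. This is an inference, but a safe one in general terms. The school professional belongs to a school that is told its arm, and the text sets no date for the judgement. If it is made after disclosure, low scorers could be removed at different rates in the two arms. Masking the analyst does not repair this, because the child has been flagged before the analyst sees the data.

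**Working it through.** **1. The plan's own figure.** Inputs from Sample size {14}: difference 0.4 SD, SD 8.32, alpha 0.05 (taken as two-sided), power 80%, ICC 0.02, 44 students per school.

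- Individually randomised: 2 × (1.960 + 0.842)² / 0.4² = 98.1, so 99 per arm.
- Design effect: 1 + (44 − 1) × 0.02 = 1.86. Then 99 × 1.86 = 184.1 per arm, and 184.1 / 44 = 4.19 schools.
- With a t reference on 2(k − 1) degrees of freedom, power is 76.9% for k = 5 schools per arm and 85.8% for k = 6. Six schools, or 6 × 44 = 264 students, is the smallest number that reaches 80%.
- Inflation: 264 / (1 − 0.10 − 0.20) = 377.1, matching 377.

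The stated figures reproduce. The allowances are 10% for refusal and 20% for loss; none is for this exclusion.

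**2. Power is not the issue.** Excluding an assumed 2%, 5% or 10% equally in both arms takes the 85.8% to 85.5%, 84.9% or 83.9%.

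**3. Bias, simple case (all rates assumed).** If excluded children lie 1.5 SD below the rest, removing a fraction f raises the arm mean by about 1.5 × f SD.

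- Equal exclusion in both arms: 1.5 × (f − f) = 0.
- 5% in one arm and 2% in the other: 1.5 × (0.05 − 0.02) = 0.045 SD, which is 0.045 / 0.4 = 11% of the target difference, or 0.045 × 8.32 = 0.37 points.

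**4. With the planned adjustment.** Section {20a} adjusts for baseline performance on the same tests. If these children are as far behind at baseline as at follow-up, and r is the baseline-outcome correlation (not given; assumed), the adjusted shift is about 0.045 × (1 − r).

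- r = 0.5: 0.0225 SD, about 6% of 0.4 SD.
- r = 0.7: 0.0135 SD, about 3% of 0.4 SD.

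**5. Outer bound.** Suppose exactly the lowest-scoring fraction f is removed in one arm only, with no true effect and no baseline adjustment. The spurious difference is φ(c) / (1 − f), where c is the f-quantile of the standard normal. The standard error at 6 × 44 is √(2 × 1.86 / 264) = 0.119 SD.

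| f | Spurious difference (SD) | Share of 0.4 SD | Two-sided type I error |
|---|---|---|---|
| 1% | 0.027 | 7% | 5.6% |
| 5% | 0.109 | 27% | 15.0% |

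If the judgement correlates only 0.5 with the score, the differences halve to 0.013 and 0.054 SD, and type I error is 5.1% and 7.4%. Type I errors use the normal approximation.

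**6. Timing and intention-to-treat.** Two cases follow from the text.

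- Status fixed before randomisation: the exclusion criterion makes the child ineligible. The child may still play with the class, but is not a trial participant, so {20a} and {20c} are satisfied.
- Status set by the undated definition after allocation: an enrolled child is removed, and {20a} and {20c} are not satisfied.

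The text does not say which case applies.

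**The case against.** The strongest reply is that these are ineligible children, described three ways. Cognitive disability is an exclusion criterion. The section on comparators explains that all children who wish to may play, to avoid discrimination, while only some are evaluated. Section {11b} calls the diagnosis previous and uses the perfect tense for the identification, which points to status that already exists. The reason given is measurement validity, and nothing says the school professional sees any test score. Evaluators are blind, and educators in both arms receive the same training, so no motive for unequal exclusion is evident. The flowchart and timeline, which might fix the order of events, are not available here.

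Much of this stands. A reader might infer that the plan contradicts intention-to-treat outright. The documents do not support that, since the conflict arises only if the undated definition is used after randomisation. A reader might also take 0.045 SD, or the 15% type I error, as the expected harm. Both rest on assumed rates and leave out the planned baseline adjustment, and the second assumes removal of exactly the lowest scorers in one arm only.

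The reply does not remove the mismatch. The section's own definition replaces a diagnosis with an opinion about the study's instruments, and the text does not say what the diagnosis must precede. The mismatch holds whatever the timing. The timing point rests on silence and should be read that way.

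**Conclusion.** The point holds in a limited form. The exclusion criteria and {11b} give rules that are not equivalent. The operative one is linked to performance on the outcome tests, and the text ties it neither to a time before the school learns its arm nor to a blinded judge. That leaves open a route to unblinded, outcome-related exclusion; it does not show that such exclusion will happen.

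The size and direction of any bias cannot be derived from the documents. It is zero under equal application. Under a modest assumed imbalance it is a few hundredths of an SD, and less after baseline adjustment. This is small beside the 0.4 SD target, but the remedy costs almost nothing and the point affects who is in the primary analysis, so it is worth changing.

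**What to change.** Use one definition in the exclusion criteria and in {11b}, and apply it as an eligibility criterion. Record the excluded children for each school on a dated list that is closed before the school is told its arm. Where that is no longer possible, have the decision made by someone blind to allocation. After that, remove no child from the analysis on this ground. In {20a} and {20c}, state that the primary analysis includes all eligible randomised children.

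The school-professional criterion need not be deleted. It may stay if it is applied before allocation is known, which respects the concern about instruments not validated for these children.

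The cost is some wording and one dated list per school. The downside is that a few children identified late stay in the analysis, with scores that the protocol regards as less reliable.

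### Section {11b} drops the data of children who leave the study, while the intention-to-treat rules in {20a} and {20c} keep those children in the primary analysis

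*Protocol article*

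**What the plan says.** Section {11b} of the protocol article gives children the right to withdraw: "they can leave the study at any time and for any reason, if they wish, without any consequences". The next sentence adds: "If children leave the study, their information and collected data will not be analysed". It sets no limit by reason, by date of leaving or by type of data.

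Section {20a} states: "The primary analysis will be conducted based on intention-to-treat". It defines that analysis as follows: "This analysis includes all randomized subjects in the groups, regardless of whether or not they complete the treatment or follow-up period". The same section makes the measurement taken after the intervention the primary one and repeats the analysis at 6, 12, 18 and 24 months.

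Section {20c} states: "Every participant randomized to the trial will enter the primary analysis". It then says that "participants who drop out prematurely, or are non-compliant with the study intervention, will be included in the primary analysis", in the group assigned at randomisation, and adds: "Multiple imputations will be used to handle missing data in the primary and secondary analyses".

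**The concern.** The two sets of rules give opposite instructions for the same child, so the primary analysis set is not defined. If nobody settles this beforehand, the choice may be made after the data have been seen.

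The rule in {11b} also reaches backwards, because it covers data already collected. Sessions last about two and a half months and follow-up lasts 24 months, so most of the time in which a child can leave comes after the primary measurement. The interim-analysis section {21b} says that data are analysed at the end of the trial. A child who leaves at month 18 would therefore lose a valid primary score before any analysis is run.

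Blinding does not prevent selective leaving. Section {17b} says that participants will know their school's allocation, and the two games differ in kind. Reasons for leaving could therefore differ between arms.

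**Working it through.** **1. The rules side by side**

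| Child | {11b} | {20a} and {20c} |
|---|---|---|
| Stays but does not comply | not addressed by the withdrawal sentence | included |
| Leaves before the primary measurement | all data removed | included, missing score imputed |
| Leaves after the primary measurement | all data removed, primary score too | included with the observed score |

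The rules cannot be separated by assigning them to different children. Section {11b} distinguishes not wanting to take part in sessions from leaving the study. Section {20c} distinguishes non-compliance from premature dropout and includes both. A child who leaves falls under both rules.

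**2. What imputation could recover**

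Section {20c} uses multiple imputation in the main analyses, while {20a} describes it as a sensitivity analysis. Under either description, imputation for a child needs that child's baseline or other scores. Section {11b} removes these as well.

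**3. The plan's own sample size**

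Inputs from the sample-size section {14}: alpha 0.05 (two-sided assumed), power 80%, SD 8.32, difference 0.4 SD = 3.33 points, ICC 0.02, 44 children per school, 10% refusal, 20% loss.

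- Individual randomisation: 2 × (1.960 + 0.842)² / 0.4² = 98.1, so 99 per group.
- Design effect: 1 + (44 − 1) × 0.02 = 1.86. Then 99 × 1.86 = 184 per group, or 184/44 = 4.2 schools.
- With a t test on 2(k − 1) degrees of freedom, power is 76.9% with 5 schools per group and 85.8% with 6. Six schools × 44 = 264, as stated.
- Inflation: 264 / (1 − 0.10 − 0.20) = 377, as stated.

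**4. How many children could be affected**

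- Refusals taken off first: 377 × 0.90 = 339. Then 339 × 0.20 = 68 leavers per group, and about 271 remain.
- Both deductions taken from 377, as the plan's inflation implies: 377 × 0.20 = 75 leavers, and 377 × 0.70 = 264 remain.

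These are upper figures. They treat the whole planned loss as leaving under {11b}. In both versions the planned 264 is still met, so the issue is bias and discarded data rather than power.

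**5. Possible bias of a stayers-only comparison**

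Let p be the proportion leaving in an arm and g the stayer mean minus the leaver mean, in SD. The stayer mean exceeds the full-arm mean by p × g. The bias in the contrast is p₁g₁ − p₂g₂. All values of g, and the split of p between arms, are assumptions.

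| Scenario | Bias (SD) | Share of 0.4 SD |
|---|---|---|
| 20% leave in each arm, same gap | 0 | 0% |
| 25% v 15% leave, gap 0.25 in both | 0.10 × 0.25 = 0.025 | 6% |
| 25% v 15% leave, gap 0.50 in both | 0.10 × 0.50 = 0.05 | 12.5% |
| 20% leave in each arm, gap 0.25 in one arm only | 0.20 × 0.25 = 0.05 | 12.5% |
| Same, gap 0.50 | 0.10 | 25% |
| Same, gap 0.75 | 0.15 | 37.5% |

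The direction depends on which arm has the larger product. The figures are unadjusted.

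**The case against.** The strongest defence is that the statistical sections should govern. Both include dropouts explicitly, and an analyst who followed them would never run a stayers-only analysis. The {11b} sentence comes directly after the right to leave, so it may have been meant only for families who withdraw consent to the use of their data. That is a reasonable guess at the intention, but the text does not state that limit or give an order of precedence. The contradiction stands.

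The defence does succeed against three stronger readings.

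- A reader might infer that the trial is designed as a stayers-only comparison. That follows only if {11b} prevails, which the article does not say.
- A reader might take 12.5% to 37.5% of the target effect as the expected distortion. That range needs all of the 20% loss to be active leaving, with a score gap in one arm and none in the other. The documents support neither assumption. Passive loss, such as changing school, need not count as leaving, and {14} gives no split. The primary model also adjusts for baseline score, age, gender and mental health, which would absorb part of any gap that these predict.
- Section {11b} also excludes children with cognitive disability, described as "identified by a trained school professional indicating that they cannot clearly understand the instructions of the instruments". A reader might infer that school staff make this judgement after learning their allocation. The documents do not say so. Reported cognitive disability is an exclusion criterion in {10}, {11b} refers to a previous diagnosis, and no section places the identification after disclosure. It forms no part of this point.

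**Conclusion.** The contradiction between {11b} and the pair {20a} and {20c} is certain from the text, and it decides who is in the primary analysis. If {11b} were followed, observed primary scores would be discarded and imputation could not recover them.

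The size of any bias is not established. It runs from zero, through 0.025 to 0.05 SD under unequal leaving rates, to 0.05 to 0.15 SD in the adverse one-arm case, under the assumptions shown and before covariate adjustment. At most about 68 to 75 children per group would be affected, and possibly far fewer. The planned number analysed is not threatened. The point deserves correction because the rule is explicit, touches the primary outcome and is simple to put right.

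**What to change.** Replace the {11b} sentence with a rule such as: withdrawal ends further assessment; data collected up to withdrawal are kept and analysed in the allocated group, unless the guardian asks for their deletion. This agrees with {20a} and {20c}. Deletions on request should be counted and reported by arm.

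The change needs no new data, and 264 and 377 per group are unaffected. It is more than an edit of wording, however. The trial-status section expected recruitment to end around July–August 2022, and the article appeared in November 2022, so consent forms would probably have been signed by then. Under {25}, a substantial amendment goes to the ethics committee, and additional consent is sought where needed. Whether guardians must be asked again depends on what the consent form promised about data after withdrawal, and that form is not shown. If consent cannot be obtained for some children who have left, the number removed should be reported by arm and the primary analysis described accordingly.
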